# Effects of electroacupuncture combined with computer-based cognitive rehabilitation on mild cognitive impairment: study protocol for a pilot randomized controlled trial

**DOI:** 10.1186/s13063-019-3599-6

**Published:** 2019-08-05

**Keywords:** Mild cognitive impairment, Electroacupuncture, Computer-based cognitive rehabilitation, Randomized controlled trial, Study protocol

## Abstract

**Background:**

Mild cognitive impairment (MCI) is defined as an intermediate stage between normal aging and Alzheimer’s disease (AD), and early and easily available interventions to delay the progress of MCI to AD are necessary. Feasible complementary and alternative therapies such as electroacupuncture (EA), exercise, and cognitive training have shown some beneficial effects on MCI and AD. Here we report the protocol for a randomized controlled trial of the efficacy and safety of EA combined with computer-based cognitive rehabilitation (EA-CCR) for the treatment of MCI.

**Methods:**

The study will be a prospective, outcome assessor-blinded, parallel-arm, single-center (DongShin University Gwangju Korean Medicine Hospital, Republic of Korea), pilot randomized controlled clinical trial with a 1:1 allocation ratio. Participants with MCI will be randomized to a computer-based cognitive rehabilitation (CCR) or an EA-CCR group (*n* = 18 each). The CCR group will receive RehaCom cognitive rehabilitation once (30 min) a day, 3 days per week (excluding Saturday and Sunday) for 8 weeks. The EA-CCR group will receive EA at Baihui (GV20), Sishencong (EX-HN1), Fengchi (GB20), and Shenting (GV24) in addition to RehaCom cognitive rehabilitation once (EA:30 min, CCR:30 min) a day, 3 days per week (excluding Saturday and Sunday) for 8 weeks. The primary outcome will be an improvement in cognitive function assessed using the Korean version of the Alzheimer’s Disease Assessment Scale-cognitive subscale. Scores for the Korean version of the Montreal Cognitive Assessment scale, Center for Epidemiological Studies Depression Scale, Korean Activities of Daily Living scale, Korean Instrumental Activities of Daily Living scale, and European Quality of Life Five Dimension Five Level Scale will be recorded as secondary outcome measures. All scores will be recorded at baseline (before intervention), 8 weeks after the first intervention (i.e., at the end of the intervention), and 12 weeks after completion of the intervention.

**Discussion:**

The study is expected to provide preliminary evidence regarding the efficacy, safety, and usefulness of EA-CCR for the treatment of MCI.

**Trial registration:**

Korea Clinical Information Service, cris.nih.go.kr, KCT0003415. Registered on 4 January 2019. Retrospectively registered, http://cris.nih.go.kr.

**Electronic supplementary material:**

The online version of this article (10.1186/s13063-019-3599-6) contains supplementary material, which is available to authorized users.

## Background

Mild cognitive impairment (MCI) is defined as a slight impairment in cognitive function (typically memory) with otherwise normal function in the performance of activities of daily living. It is now widely accepted that MCI is a transitional phase between normal function and Alzheimer’s disease (AD), during which cognitive impairment is progressing [1, 2]. Population-based studies have found that the prevalence of MCI in elderly individuals (≥ 65 years) is 10–20%, with 5–10% of patients progressing to AD each year [3–5].

The US Food and Drug Administration (FDA) has not approved any therapeutic agents that could manage symptoms in the short term or prevent/slow down the progression of MCI to AD in the long term [6]. In order to decrease the prevalence of AD, there is an urgent need for novel and effective approaches for treating MCI. Therefore, various nonpharmacological treatments such as cognitive training [7, 8], physical treatment [9], and acupuncture [10–12] have been attempted.

Acupuncture is a common traditional Chinese medicine technique used for the treatment of neuropathy, with manual and electrical stimulation of acupoints being commonly used stimulation modes [13]. Recent studies have reported that acupuncture may be an effective adjunctive therapy for neurological diseases, including stroke [14], AD [15], MCI [10–12, 16], and vascular dementia [17, 18]. The potential mechanisms of action underlying its putative effects in patients with cognitive impairment include enhanced release of neurotrophic factors, decreased oxidative damage and expression of apoptosis-related genes, improved synaptic plasticity, and proliferation and survival of neuronal precursor cells in the hippocampal CA1 and dentate gyrus area [19–21]. Computer-based cognitive rehabilitation (CCR) has been widely used since its introduction in 1986, and it has been further improved with neuroscientific and technological developments [22, 23]. CCR interventions may generate some positive effects in patients with MCI and/or dementia, such as an improvement in learning and short-term memory and amelioration of behavioral symptoms [8]. RehaCom (Hasomed Inc., Magdeburg, Germany, http://www.hasomed.de) is a software package that has been translated into different languages, including Korean. This software includes five different therapeutic programs that seek to restore attention, memory, executive functions, and the visual field. Each program has one to four different tasks from which participants can choose during each therapy session. Because RehaCom provides a battery of standardized tasks with immediate feedback, it is useful for follow-up examinations and clinical studies as well as the treatment of MCI [23].

Although electroacupuncture (EA) is used for the treatment of MCI in Korean medicine, evidence regarding its efficacy is insufficient. Here we describe the protocol for an outcome assessor-blinded, parallel-arm, pilot randomized controlled clinical trial of the efficacy and safety of EA combined with CCR (EA-CCR) for the treatment of MCI. The results of the study are expected to provide preliminary evidence regarding the usefulness of EA-CCR for patients with MCI.

## Methods/design

### Objective

This study will investigate the efficacy of EA-CCR for the treatment of MCI through a comparison of the effects of EA-CCR with those of CCR in terms of an improvement in cognitive function in patients with MCI.

### Hypothesis

The null hypothesis is that the improvement in cognitive function achieved with EA-CCR is not superior to that achieved with CCR in patients with MCI.

### Study design

The study design is in accordance with the Standard Protocol Items: Recommendations for Interventional Trials (SPIRIT) and Consolidated Standards of Reporting Trials (CONSORT) 2010 guidelines [24, 25] (see Additional file 1). The study is a prospective, outcome assessor-blinded, parallel-arm, single-center (DongShin University Gwangju Korean Medicine Hospital, Republic of Korea), pilot randomized controlled clinical trial with a 1:1 allocation ratio. A total of 36 participants who meet the inclusion and exclusion criteria will be randomly allocated to an EA-CCR or a CCR (*n* = 18 each) group. Participants in the CCR group will receive RehaCom cognitive rehabilitation only, while those in the EA-CCR group will receive EA at Baihui (GV20), Sishencong (EX-HN1), Fengchi (GB20), and Shenting (GV24) along with RehaCom cognitive rehabilitation. The treatment duration will be 8 weeks in both groups. The primary outcome measure will be an improvement in cognitive function evaluated using the Korean version of the Alzheimer’s Disease Assessment Scale-cognitive subscale (ADAS-K-cog). The secondary outcome measures will include changes in scores for the Korean version of the Montreal Cognitive Assessment (MoCA-K) scale, Center for Epidemiological Studies-Depression Scale (CES-D), Korean Activities of Daily Living (K-ADL) scale, Korean Instrumental Activities of Daily Living (K-IADL) scale, and European Quality of Life Five Dimension Five Level Scale (EQ-5D-5 L). All scale scores will be recorded at baseline (before intervention), 8 weeks after the first intervention (i.e., at the end of the intervention), and 12 weeks after completion of the intervention.

This study protocol complies with the principles of the Declaration of Helsinki and Korean Good Clinical Practice guidelines and has been approved by the Ministry of Food and Drug Safety (Medical Device Clinical Trial Plan approval number 859). The trial has been registered at cris.nih.go.kr (registration number, KCT0003415). The study design is summarized in Figs. 1 and 2.

**Fig. 1 Fig1:**
[figure not shown]
Study design flow chart

**Fig. 2 Fig2:**
[figure not shown]
Standard Protocol Items: Recommendations for Interventional Trials (SPIRIT) figure showing the schedule of enrollment, interventions, and data collection

### Participant recruitment

Participants will be recruited at DongShin University Gwangju Korean Medicine Hospital, Republic of Korea. The study will be advertised through local newspapers, the Internet, and posters in communities and hospitals. Individuals can enquire about participation through the telephone or personal visits. When interested individuals visit the clinical research center at DongShin University Gwangju Korean Medicine Hospital, they will receive an explanation about the study from the clinical research coordinator (CRC) and will be requested to voluntarily sign an informed consent form before participation. All recruited individuals will be screened by the Korean version of the Mini-Mental State Examination (K-MMSE) and MoCA-K for confirmation that all inclusion criteria are met. The CRC will continuously monitor the medical condition of the enrolled participants to ensure adherence to the intervention protocols.

### Inclusion criteria

Participants meeting all of the following criteria will be included in the study: (1) age 55 to 85 years; (2) fulfillment of the Petersen diagnostic criteria for MCI [1, 2] with memory impairment for at least 3 months, (3) K-MMSE score of 20–23, (4) MoCA-K scale score of 0–22, (5) Korean language fluency that is adequate for reliable completion of all study assessments, and (6) voluntary provision of informed consent.

### Exclusion criteria

The exclusion criteria are as follows: (1) diagnosis of dementia according to the Diagnostic and Statistical Manual of Mental Disorders-IV; (2) history of structural brain lesions that can cause cognitive impairment, such as traumatic brain injury, stroke, intracranial space-occupying lesions, and congenital mental retardation; (3) presence of cancer and/or serious cardiovascular, cerebrovascular, liver, or kidney disease; (4) history of treatment for alcohol or drug dependency or mental diseases such as schizophrenia, serious anxiety, or depression in the past 6 months; (5) ongoing treatment for MCI, such as medication, acupuncture, or cognitive training); (6) difficulties in assessment due to visual and hearing impairments; (7) presence of contraindications for EA, such as blood clotting abnormalities (e.g., hemophilia), infection of the skin over the head, or the presence of a pacemaker); and (8) concurrent participation in other clinical trials.

### Ethical considerations

This study has been approved by the institutional review board (IRB) of DongShin University Gwangju Korean Medicine Hospital, Republic of Korea. The purpose and potential risks of this clinical trial will be fully explained to the participants and their families. All participants will be asked to provide written informed consent before participation.

### Randomization

Following the acquisition of written informed consent, the practitioners who will perform the intervention will conduct a screening interview. Then, the assessor will perform baseline measurements for participants who meet the inclusion criteria. The 36 enrolled participants will be immediately assigned serial numbers generated using SPSS version 21 software (IBM Corp., Armonk, NY, USA) and randomly allocated to one of the two study groups (*n* = 18 each). The serial number codes will be inserted into opaque envelopes that will be sealed and stored in a double-locked cabinet; these will be opened by the principal investigator (PI) or practitioners, who will perform the intervention in the presence of the patient and a guardian.

### Implementation

The CRC will generate the allocation sequence, enroll participants, and assign participants to the intervention.

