### Statistical analysis

A statistician who is not involved in the clinical trial will analyze the final data. We will perform a per-protocol analysis (PP group) for the assessment of efficacy with a supplementary full analysis set (FA group). We will compare the results of analyses between the PP and FA groups and confirm whether there are statistically significant differences between the two groups. If there is a significant difference, the cause will be reviewed and reflected in the efficacy assessment. All statistical analyses will be performed using SPSS version 21 software (IBM Corp.).

Baseline characteristics will be described and compared. Continuous data will be presented as means and standard deviations and compared using the independent *t* test or Wilcoxon rank sum test, while categorical data will be presented as frequencies and percentages and compared using the chi-squared test or Fisher’s exact test.

Changes in scores for the ADAS-K-cog, MoCA-K scale, CES-D, K-ADL scale, K-IADL scale, and EQ-5D-5 L at 8 weeks (at the end of the intervention) and 20 weeks (12 weeks after the end of the intervention), relative to the baseline score, will be analyzed for each group using the paired *t* test or Wilcoxon signed rank test. The degree of changes at each time point will be evaluated using repeated measures analysis of variance and the two-sample *t* test or Wilcoxon rank sum test. Subanalyses will be applied to the statistical analysis according to the participant age. All reported *P* values will be two-sided with confidence intervals at the 95% levels. A *P*value of < 0.05 will be considered statistically significant.

Data for participants who meet the dropout criteria (i.e., < 75% compliance with the protocol procedures [received less than 18 of the 24 scheduled treatment sessions], incidence of SAEs, reluctance to continue the trial, incomplete data that could influence the trial, large error in protocol or significant deviation in implementation, or decision to terminate trial participation by the PI or IRB) will be excluded. Missing values will be implemented by the last observation carried forward method. Interim analyses will not be performed.

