### Confidentiality and data management

All identification records of the participants will be kept confidential. When the results of the study are published, the identification records can be accessed under IRB approval. All documents related to the trial, including CRFs, will be recorded and labeled with participant identification codes and will not reveal the name of the participant. These serial number codes will be stored in sealed, opaque envelopes and kept in a double-locked cabinet. All participant data will be recorded in Excel files by the CRC, and these electronic data will be stored in a password-protected computer. Individuals who are not authorized by the IRB cannot access the data. In addition, raw data (CRFs) will be stored in a cabinet until the end of the study. Written informed consent for the publication of individual details and accompanying images will be obtained from the participants.

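### The coordinator who enrols participants also generates the allocation sequence, so allocation is not concealed from the enroller in an open-label trial of 18 per arm

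*Protocol article*

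**What the plan says.** The Implementation section is a single sentence: "The CRC will generate the allocation sequence, enroll participants, and assign participants to the intervention". Participant recruitment adds that the CRC explains the study to interested people at the visit where they are asked for consent.

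Randomization describes the concealment device: "The serial number codes will be inserted into opaque envelopes that will be sealed and stored in a double-locked cabinet". It then says of the envelopes that "these will be opened by the principal investigator (PI) or practitioners". It also says that "the practitioners who will perform the intervention will conduct a screening interview", and that the assessor takes baseline measurements before allocation. The article mentions SPSS-generated serial numbers and 18 participants per group, and no blocking.

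No section withholds the list from the CRC or separates generating the sequence from enrolling. Against selection bias, the Blinding section relies on choosing staff without conflicts of interest or fixed views. The Discussion acknowledges that acupuncturists and participants are not blinded. For the final analysis, the Statistical analysis section says: "A statistician who is not involved in the clinical trial will analyze the final data".

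**The concern.** Concealment means that whoever decides if and when a candidate enters cannot know the assignment that comes next. Here one role creates the list and also enrols. That person could, knowingly or not, encourage, delay or discourage a candidate according to the coming assignment.

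The other safeguards do not reach this. Assessor blinding deals with how outcomes are measured, not with who enters which arm. Envelopes protect against people who have not seen the list. An undertaking about staff attitudes is not a procedural control. An independent monitor checks documents, but selective timing of enrolment need not leave a trace in them. Analysis cannot reliably undo the bias, because the prognostic impressions behind it may not be measured.

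The pilot label does not remove the issue. The article sets up a superiority hypothesis, tests at P < 0.05, and offers the result as preliminary evidence of efficacy and a foundation for further research.

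A second problem is one of consistency: under Randomization the PI or practitioners open the envelopes, while under Implementation the CRC assigns.

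**Working it through.** The plan gives no effect size, SD or power (Sample size estimation calls 18 per group a pragmatic pilot size), so there is no stated figure to reproduce. The totals agree: 18 + 18 = 36.

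**Who can know the next assignment**

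| Role | Tasks stated | Hidden by the envelopes? |
|---|---|---|
| CRC | Explains study, generates sequence, enrols, assigns | No: author of the list |
| Practitioners | Screening interview; may open envelopes | Yes, until opened |
| PI | May open envelopes | Yes, until opened |
| Assessor | Baseline before allocation; later assessments | Yes |

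Concealment fails for one role, and it is the role that enrols.

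**How much the list adds to guessing**

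Assumption: a simple random ordering of 18 and 18, with past assignments known because the trial is open. Always guessing the arm with more places left gives an expected number of correct guesses of

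n + 2^(2n−1)/C(2n, n) − 1/2, with n = 18.

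- 2^35 / C(36, 18) = 34,359,738,368 / 9,075,135,300 = 3.786
- 18 + 3.786 − 0.5 = 21.29 of 36, or 59%. A simulation gave 21.27.
- With the list in hand: 36 of 36, or 100%.

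The same formula per block shows what small blocks would do:

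- Blocks of 4 (n = 2): 2 + 8/6 − 0.5 = 2.83 of 4, or 71%.
- Blocks of 6 (n = 3): 3 + 32/20 − 0.5 = 4.10 of 6, or 68%.

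**What a given bias would do to the test**

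With 18 per arm, the SE of a mean difference is SD × sqrt(2/18) = 0.333 SD. If selection shifts the difference by b SD and treatment has no effect, the two-sided rejection rate at 0.05 (normal approximation) is

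Φ(b/0.333 − 1.96) + Φ(−b/0.333 − 1.96).

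| Assumed b (SD) | False-positive rate |
|---|---|
| 0 | 5.0% |
| 0.1 | 6.0% |
| 0.2 | 9.2% |
| 0.3 | 14.7% |
| 0.5 | 32.3% |

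For scale, exchanging one participant between arms for another who differs by 1 SD moves one mean by +1/18 and the other by −1/18, so the difference moves by 2/18 = 0.11 SD. A gap of 2 SD gives 0.22 SD. The values of b and these exchanges are assumptions, not figures from the article.

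**The case against.** The strongest reply is that the plan does have concealment: sealed opaque envelopes, a double-locked cabinet, and opening by people other than the CRC. The CRC's discretion is also limited. Practitioners conduct the screening interview, entry depends on numeric K-MMSE and MoCA-K limits, and the assessor takes baseline first. Recruitment is planned from 29 November 2018 to the end of June 2020, about 19 months for 36 people or roughly two a month, so there will seldom be several candidates whose order could be changed. Outcomes are analysed as change from a pre-allocation baseline, which deals with part of any imbalance in measured severity. Nothing says the CRC keeps or consults the list.

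Much of this stands as a limit on the size of the risk. It does not remove the risk, because the CRC still explains the study, still enrols, and is nowhere barred from the list.

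Some stronger readings are tempting but not supported:

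- **That allocation is not concealed at all.** The envelopes can conceal it from the PI and practitioners.
- **That practitioners who screen and also open envelopes are a further breach.** Randomization places allocation after screening and baseline, and in that order the overlap does no harm.
- **That the CRC's recording of adverse events and data entry is a consequence of this flaw.** Generating the list does not create that issue, and moving the list elsewhere would not change it in a trial where participants and practitioners are unblinded.

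The difference between Randomization and Implementation may be loose wording, with one describing the opening of an envelope and the other the administration of assignment. It still needs to be reconciled.

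**Conclusion.** The point holds for the CRC. As written, the person who enrols also authors the sequence, so allocation is not concealed from the enroller. This is a procedure the article states, not a detail left to a fuller document, and it deserves correction while recruitment continues.

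The contrast in predictability is 100% against about 59%. The 59% rests on an assumed simple 18:18 rule with past assignments known; the 100% rests on the CRC having access to the list. The rise in false positives from 5% to about 9–15% rests on an assumed bias of 0.2 to 0.3 SD and only illustrates sensitivity at this sample size.

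A reader might infer that randomisation has failed, or that protection against confounding is lost. The article does not support that: allocation is still described as random, and what is shown is an opening for bias, not its occurrence.

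**What to change.** For participants still to be randomised:

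1. Have someone with no participant contact generate the remaining sequence and prepare sequentially numbered, sealed, opaque envelopes. This could be an existing staff member outside recruitment, treatment and assessment. It could be the statistician only if the independence wording in Statistical analysis is amended, since generating the list would be involvement in the trial.
2. Randomly order the places left in each arm so that the totals of 18 and 18 are kept, and avoid small blocks. A short or unequal remainder is easier to guess than a full list, so the change should be made soon.
3. Withhold the list from the CRC, PI, practitioners and assessor. The CRC then only enrols.
4. Open each envelope only after eligibility and baseline are recorded and the participant's identification code is written on it. Use the code, not the name, in keeping with Confidentiality and data management.
5. Rewrite Randomization and Implementation so that both name the same role for generating, enrolling, opening and assigning.
6. Report how many participants were allocated before the change.

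The cost is a small amount of staff time and an amendment, which Quality assurance says requires approval from both the Ministry of Food and Drug Safety and the IRB. The sample size does not change. Participants already randomised are not protected, which is why their number should be reported.
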